### Power Calculation

We conducted a Monte Carlo simulation study to determine the necessary number of individuals to randomize (N). We deliberately focused on the total weekly consumption outcome, as the analysis of this outcome in general requires more individuals than does the analysis of heavy episodic drinking (because of higher variance). We will begin by describing the initial distributional assumptions that we made and then the result of the simulations. We aimed to achieve 0.8 power at the .05 significance threshold.

The effect (γ) of the intervention, that is, the percentage reduction in mean total weekly alcohol consumption in the intervention group, is assumed to follow a beta distribution with mean 0.15 and SD 0.025.The mean number of standard units consumed in the control group (μ_C_) at follow-up is assumed to follow a normal distribution with mean 10 and SD of 0.5. The population under analysis are risky drinkers, thus, a mean consumption of 10 standard units is appropriate, and the analysis is quite robust to moderate changes in this assumption.The mean number of standard units consumed in the intervention group (μ_I_) at follow-up is assumed to follow a normal distribution with mean (1-γ)_C_ and SD of 0.5.The distribution over the number of standard units consumed at follow-up for both the intervention and control group is assumed to follow a negative binomial distribution. The means of these distributions are given by μ_C_ and μ_I,_ respectively, and have a dispersion parameter θ sampled from a normal distribution centered at 1 with an SD of 0.05.The number of individuals allocated to the intervention group follows a binomial distribution, with a 0.5 probability of success over N trials.

The Monte Carlo simulation explored different values of N (number of individuals randomized). For each N explored, the following simulations were done:

Draw 1 sample each for γ, μ_C_, μ_I,_ and θAllocate a random number of individuals to the interventionGive each individual a number of standard units consumed following the negative binomial distribution appropriate for their respective groupsAnalyze the data using negative binomial regressionNote if the 0.05 threshold has been broken for the group allocation coefficient in the regression modelRepeat 100 times from (a) and then calculate power as the percentage of times that the threshold was brokenRepeat 1000 times from (1) and calculate the average power from (e)

We found that for N=1800; we have an expected average power of 0.79.

In previous studies similar to this [24,65], we have been able to achieve more than 90% response rate at follow-up using the scheme described in the section Follow-up Attempts. Assuming that the response rate is lowest at 4 months and that it follows a beta distribution with mean 85% and an SD of 5% (giving a 95% credible interval between 75% and 94%), then we will expect to lose 326 individuals to follow-up (interquartile range: 231,398). This implies that we need to randomize approximately 2126 individuals (interquartile range: 2031, 2198).

## Results

Participant recruitment is planned to begin in April 2019 and last for a maximum of 24 months. The first dataset will be available approximately 2 months after the final participant has been recruited, and the final dataset will be available approximately 2 months later. No participants had been recruited at the time of submitting this protocol.

## Discussion

### Principal Findings

In Sweden, the student health care centers routinely administer eSBIs (via email) to the university students that they serve [7,8], and the general public have access to eSBIs via websites (eg, livsstilsanalys.alexit.se). However, beyond this single session intervention, there are no evidence-based digital interventions available for those who need continued support, despite the ubiquitousness of mobile phones in Sweden. The advice for individuals who need support beyond the eSBI is generally to search for advice on health websites or to seek help at a primary health care center.

This study is an evaluation of whether or not access to the novel intervention has any effect on alcohol consumption outcomes compared with providing information including referring individuals on to an alcohol and health website. If found effective, this type of intervention has the potential to reduce the burden from negative consequences of excessive alcohol consumption for individuals who need support beyond a single session eSBI and has been designed to have potential for extensive reach among those who may benefit. It has also been designed so that individuals can choose how long they use it for, meaning that intervention exposure can potentially extend for many years.

Previous trials of mHealth interventions targeting alcohol consumption have been aimed toward specific subgroups of a population, quite often young adults or individuals in alcohol use disorder treatment programs. Many of the studies have had issues with trial design or execution, and therefore, the collective evidence for mHealth interventions’ effect on alcohol consumption is not well-developed. The novelty of targeting the adult population of Sweden by means of a broader recruitment than in previous trials, in the ways proposed, allows for both primary prevention: helping individuals prevent negative consequences, and secondary prevention: helping individuals to reduce negative consequences already experienced. By using a scheme that we have previously found successful in achieving high follow-up rates, we aim to avoid the attrition issues that have manifested in previous studies.

### Substudies

Apart from the main outcome, this trial will also investigate methodological and ethical issues in randomized controlled trials. Although informing participants about trial procedures before asking for informed consent has been required for some time, the introduction of GDPR has increased the focus on data privacy and handling of personal information. Participants should be made aware of their rights, and the findings from the substudy regarding recall of trial procedures will give insights into how well participants read, and later recall, the information given before informed consent. If individuals cannot recall that randomization was to occur, the ethical implications deserve fuller consideration.

Similarly, we will explore the nature of the alcohol information control condition and the extent to which introductory text has implications for accessing further information via a link. This study is informative about the inter-related issues of the possible effects of contrasting types of information and the nature of control conditions, which commonly employ informational content.

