#### Randomization

In all cases, randomization will be fully computerized, will not employ any strata or blocks, and will not be possible to subvert as this and all subsequent study processes are fully automated. The main study will be single-blind as participants will be aware that 2 settings exist, and they will know which one of them they have been allocated to (intervention or control). The substudies involving Consent-1, Consent-2, Info-1, and Info-2 will be double-blind as participants will not be aware of the existence of the substudy or that they have been randomized. It is not possible to blind the individual responsible for data analysis, as this individual will also be responsible for data collection and involved in the monitoring of the technical platform.

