#### Follow-Up

At 1 month after randomization, an SMS message will be sent to both intervention and control with a hyperlink to a questionnaire exploring mediators. At 2 and 4 months after randomization, an SMS message will be sent to both intervention and control with a hyperlink to a questionnaire exploring alcohol consumption. At 2 months after randomization, the questionnaire exploring recall of trial procedures will be added for both groups. At 4 months after randomization, the intervention group will receive questions regarding the usability and their experiences of the intervention, and the control group will receive questions regarding their experiences of being allocated to the control condition.

Figures 3 and 4 offer an overview of the design in the form of a Standard Protocol Items: Recommendations for Interventional Trials figure and Consolidated Standards of Reporting Trials flowchart.

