**Exploratory Hypotheses**
6. Alcohol consumption will differ between groups Consent-1 and Consent-2 at 2 and 4 months after randomization. The 2-month interval will be primary.7. Alcohol consumption will differ between groups Info-1 and Info-2 at 2 and 4 months after randomization. The 2-month interval will be primary.

With regard to recall of trial procedures, there are 3 parameters that are of interest. First, participants will be asked if they recall receiving information about allocation to 2 different groups. As information regarding group allocation was presented identically for Consent-1 and Consent-2, this question will both work as a check that randomization succeeded and as a general baseline for recall regardless of group allocation. Second, participants will be asked if they recall how personal data will be handled in the study and their rights to these data. Finally, participants will be asked if they remember how the data would be analyzed and results communicated (see Multimedia Appendix 3).

We wish to measure if participants access further health-related information after reading a short SMS with basic information about short-term and long-term consequences of alcohol consumption. A proximal outcome of this is to measure whether or not participants in Info-1 and Info-2 request more information by following the included hyperlink. In addition, a short questionnaire at 4-month follow-up will investigate the control group participants, which will be used to investigate further differences between Info-1 and Info-2 (see Multimedia Appendix 3).

The acceptability and usability of the intervention will be measured through a questionnaire and the system usability scale [57] at 4-month follow-up (see Multimedia Appendix 3). The system usability scale comprises 10 Likert items exploring users’ perception on usability of a product or service.

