### Follow-Up Attempts

There are 3 follow-up stages: 1, 2, and 4 months after randomization. All follow-ups will be initiated by sending SMS messages to participants with hyperlinks to questionnaires. In all cases, the following attempts will be made to collect data from nonresponders:

A total of 2 reminders will be sent 2 days apart to those who have not responded.If no response is given to (1), then we will send questions directly in an SMS message, asking participants to respond directly with an SMS (no hyperlink).At 1 month, we will ask all 3 mediator questions.At 2 and 4 months, we will only ask for primary alcohol outcome measures.If there is no response given to (2), we will attempt to call participants to collect responses to the same questions as in (2). A maximum of 5 attempts will be made.

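### The recall substudy can show delayed recall among web responders, but not how well the consent text was read, and it shows only weakly whether people knew allocation was by chance

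*Protocol article*

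**What the plan says.** In the Discussion, Substudies, the article states that the findings "will give insights into how well participants read, and later recall, the information given before informed consent". The next sentence reads: "If individuals cannot recall that randomization was to occur, the ethical implications deserve fuller consideration".

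The measurement is set out in three places in Methods.

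- **Timing (Follow-Up):** "At 2 months after randomization, the questionnaire exploring recall of trial procedures will be added for both groups". No other recall measurement, and no measure of reading at consent, is described.
- **Item (recall paragraphs that follow the hypotheses textbox):** "participants will be asked if they recall receiving information about allocation to 2 different groups". Because this information was presented identically in both consent modes, "this question will both work as a check that randomization succeeded and as a general baseline for recall regardless of group allocation". Two further items cover the handling of personal data, and the analysis and communication of results. The questions themselves are in Multimedia Appendix 3, which is not shown.
- **Mode (Follow-Up Attempts):** the initial message and two reminders link to the web questionnaire. For the direct SMS step that follows, "At 2 and 4 months, we will only ask for primary alcohol outcome measures". The phone calls repeat those same questions.

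Under Randomization, the article says of the main trial that "participants will be aware that 2 settings exist, and they will know which one of them they have been allocated to". Recall is a secondary outcome for hypotheses 3 and 4 and is compared between Consent-1 and Consent-2 with chi-square or Fisher exact tests.

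**The concern.** The Discussion names two things, reading and later recall, and the design measures one. It also ties an ethical remark to recall of randomization, while the item as described concerns the existence of 2 groups. The Introduction, in its section on data protection and recall, lists allocation by means of randomization among the ideas that are hard to convey. Someone may remember 2 groups and still believe they were placed by need or by choice.

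Who answers also matters. Anyone who responds only by SMS or phone contributes alcohol outcomes but no recall data. Statements about participants in general would then rest on those who completed the web form.

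At stake is how a reassuring result would be read. A high proportion recalling the 2 groups could be taken to mean that the consent text was read and randomization understood. The design supports neither inference well. The primary alcohol analysis is not affected.

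**Working it through.** The article states no numerical target or expected value for recall, so there is no figure of the plan's own to reproduce. All shares below are assumptions chosen to show the range.

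**1. Reading against forgetting.** If recall can come only from text that was read and retained, then

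observed recall = share who read × share of readers who retain.

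- 60% read, 90% retain: 0.60 × 0.90 = 0.54
- 90% read, 60% retain: 0.90 × 0.60 = 0.54

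Two very different reading rates give the same 54%. A larger sample does not separate them, because one measurement cannot identify two quantities.

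**2. Later knowledge and the allocation item.** By 2 months, participants know which of the 2 settings they are in. Under Intervention and Control Conditions, controls have also been advised of a 4-month initial phase before they get the tool. Let x be the share who truly recall the consent information and c the share of the rest who answer yes from later knowledge:

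apparent recall = x + (1 − x) × c.

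With 40% reading and 30% of them retaining, x = 0.40 × 0.30 = 0.12. With c = 0.60, apparent recall is 0.12 + 0.88 × 0.60 = 0.648, about 65%. With c = 0 it is 12%. The article gives no means of telling where c lies. Even a genuine yes concerns 2 groups, not chance.

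**3. Web responders against all randomized.** Let w be the share answering on the web, p recall among them and q recall among the rest:

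overall recall = w × p + (1 − w) × q.

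Without any assumption on q, this lies between w × p and w × p + (1 − w). The excess of the reported figure over the overall value is (1 − w) × (p − q). With p = 0.80:

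| w | Bounds on overall recall | Excess if q = 0.60 | Excess if q = 0.40 | Excess if q = 0.80 |
|---|---|---|---|---|
| 0.40 | 0.32 to 0.92 | 0.12 | 0.24 | 0 |
| 0.60 | 0.48 to 0.88 | 0.08 | 0.16 | 0 |
| 0.70 | 0.56 to 0.86 | 0.06 | 0.12 | 0 |
| 0.85 | 0.68 to 0.83 | 0.03 | 0.06 | 0 |

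For the row w = 0.60: 0.60 × 0.80 = 0.48, 0.48 + 0.40 = 0.88, 0.40 × 0.20 = 0.08 and 0.40 × 0.40 = 0.16.

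The 85% mean response rate in the Power Calculation pools web, SMS and phone, so it is not the response rate for recall. The last row would apply if every responder at that rate used the web form.

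**The case against.** The strongest defence is that reading is nowhere an aim, hypothesis or outcome. The Aims and hypothesis 4 concern recall and whether it differs between two modes of presentation. Both modes are asked after the same delay, so a difference in delayed recall is the target whether it arises through reading or through retention. This stands. The allocation item is not the comparative measure either, because that information was identical in both modes. The two items that can differ by mode are untouched by the point about chance allocation.

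Three stronger readings are tempting, and the documents do not support them.

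- *That the questionnaire can show nothing of what is promised.* Later recall is part of the promise, and it is measured among web responders.
- *That recall is overstated.* Web-only response and later knowledge plausibly push it upward. But the article gives neither a web share nor recall rates, and if the others recall equally well the response bias is zero.
- *That an ethical conclusion is unsupported.* None is drawn. The sentence is conditional and is triggered by poor recall, and upward bias makes that trigger harder to meet, not easier.

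Missing data are also not ignored. Statistical Analysis Methods plans a comparison of responders with nonresponders at baseline and multiple imputation of missing outcomes. Recall is not named there, and standard imputation assumes data are missing at random, an assumption the article itself sets out to probe. This reduces the third problem without removing it.

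Finally, Limitations calls the substudies preliminary, exploratory and not powered. That limits the weight of the point, but the label concerns precision and does not supply a measure of reading. The exact item wording is not visible, so the criticism of the item applies only to the article's description of it.

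**Conclusion.** The point holds in a limited form. The statement about reading is not supported by the described design, because a single measurement at 2 months cannot separate unread from forgotten text. The allocation item, as described, is open to knowledge gained after consent and does not establish that people knew allocation was by chance. Absolute recall levels describe web responders only.

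The size cannot be fixed from the article. With an assumed 80% recall among web responders, the excess over the all-randomized value is 3 to 24 points for web shares of 85% down to 40% if the others recall at 40% to 60%, and zero if they recall equally.

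The consequence is asymmetric. Good recall of allocation would be weak reassurance, whereas poor recall would remain informative. Comparing Consent-1 with Consent-2 on data handling and on analysis and communication stays interpretable as delayed recall among those who enrolled and answered on the web.

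**What to change.** 1. Unless Multimedia Appendix 3 already does so, word the allocation item to ask how people were put into the groups, with options such as by chance, by need, by own choice and do not know. Base any statement about recall of randomization on that answer.
2. In the Discussion, limit the claim to delayed recall at 2 months among web responders and delete the part about how well the information was read.
3. Beside the web-responder figure, report recall over all enrolled participants in each consent mode, with a lower bound that counts non-answerers as not recalling (number recalling divided by number enrolled in that mode).

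The cost is one reworded item, one extra table and a less favourable recall figure. The article says no participants had been recruited at submission, so the item could be changed before first use. No measure of reading is proposed: it would mean collecting more data before consent, and Ethical Concerns already treats data collection without consent in this substudy as sensitive.

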### Ethical Concerns

The conduct of the substudies raise ethical issues, as they do not themselves involve informed consent. The possible importance of each substudy provides 1 possible justification for not seeking consent, as seeking consent would interfere with the substudy itself. The consent study also involves data collection from those who choose not to participate in the trial. A key consideration in such a situation is the possibility of harm to participants [66]. In this instance, not obtaining informed consent is regarded as being unlikely to produce harm in each substudy.

A further ethical risk lies in the nature of the control condition and its appropriateness for those who have been targeted for recruitment because they wish to drink less. Ethical considerations led us to construct the control condition, and the information contained within each arm, to resemble content that is available on the Web that study participants may encounter. The control condition is thus similar to usual care. Note, however, that this is not a population that is defined by the existence of problems or has been identified as seeking help to reduce problems, beyond responding to Web advertisements. For those participants who are drinking harmfully or seeking further help, the control condition refers on to the national Swedish Web resource.

### Limitations

The trial is designed to recruit enough participants to power the main alcohol-related outcomes; thus, the included substudies are not powered to detect significant differences. Rather, the substudies included herein are supposed to be seen as preliminary and exploratory work laying a basis for future trials of these phenomena.

The power calculation considers a range of follow-up rates (beta distribution with a mean of 85% and an SD of 5%), and the number of individuals (n=2126) found to be necessary to randomize may have to increase toward the upper quartile (n=2198) if follow-up rates are found to be lower than the mean of 85%. Our previous trials [24,65] have been able to collect data from more than 90% of participants using the same follow-up scheme used in this trial; thus, despite not using incentives to sustain high levels of follow-up rates, we believe our expectation of 85% follow-up rate to be warranted.

## Appendix

Multimedia Appendix 1 Information regarding trial procedures.

Multimedia Appendix 2 Group information.

Multimedia Appendix 3 Questionnaires.

## Abbreviations

BCT: behavior change technique
eHealth: electronic health
eSBI: electronic screening and brief intervention
GDPR: General Data Protection Regulation
MAR: missing at random
mHealth: mobile health
OR: odds ratio
SMS: short message service
